### Statistical analyses

Statistical analyses will be conducted on both per protocol (PP) and intention-to treat (ITT) bases. For the PP analysis, all participants who completed the study will be included to evaluate the primary and secondary outcomes. For the ITT analysis, all participants who were enrolled and randomized to one of the two groups will be included.

The baseline characteristics and laboratory data will be presented as the means and standard deviations for continuous variables and as frequencies and percentages for categorical variables. The incidence of AKI will be compared between the two groups using a *χ*^2^ test. The differences in changes in SCr levels and in the eGFR will be analyzed using Student’s *t*-test or the Mann-Whitney *U* test. A value of *P* < 0.05 will be considered statistically significant. All analyses will be performed using SPSS Statistics software V21.0 (IBM Corporation, Armonk, NY, USA).

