### Treatments

A selective DPP4 inhibitor, gemigliptin, which is clinically available, will be used in this study. The gemigliptin and placebo tablets will be provided by LG Life Sciences (Seoul, Korea). After randomization, the participants will take either a gemigliptin (treatment group) or placebo (control group) pill for 8 days starting 1 day before cisplatin treatment. The tablet shapes and packaging of the placebo pills are identical to those of the gemigliptin pills. The prescription and administration of the study drugs will be conducted in a double-blind manner. Based on a study that reported a renoprotective effect of a DPP4 inhibitor in a mouse model of cisplatin-induced AKI [29], 100 mg/day of gemigliptin will be administered to the participants in two divided doses for 8 days starting 1 day before cisplatin treatment (Fig. 2). The administration of other nephrotoxic drugs, such as NSAIDs, aminoglycosides, colistin, and vancomycin, will be prohibited during the study, and exposure to contrast media during the 72 h prior to treatment will result in exclusion from the study. Investigators or research coordinators will evaluate drug compliance by counting pills, and participants with less than 80 % compliance will be removed from the study.

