### Sample size calculations

No previous study has evaluated the effect of a DPP4 inhibitor on cisplatin-induced AKI. We expect that the incidence of AKI will be 25 % in patients treated with a single dose of cisplatin and that treatment with a DPP4 inhibitor could reduce this incidence by 60 %. We calculated the required sample size for an estimated dropout rate of 20 %, a one-sided level of significance of α = 5 %, and a power of 80 % and found that 91 participants will be needed in each group to find a significant difference using a *χ*^2^ test. A total of 182 participants will be included in the analysis.

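### AKI is tested in both the per-protocol and the intention-to-treat set at the same P < 0.05, with neither named primary and no rule for when they disagree

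*Protocol article*

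**What the plan says.** All references are to the protocol article.

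- **Statistical analyses** states: "Statistical analyses will be conducted on both per protocol (PP) and intention-to treat (ITT) bases". The two sets are then defined: "For the PP analysis, all participants who completed the study will be included to evaluate the primary and secondary outcomes", and "For the ITT analysis, all participants who were enrolled and randomized to one of the two groups will be included". AKI is compared between arms with a χ² test. A single rule, P below 0.05, "will be considered statistically significant". The section states no order between the sets, no requirement that both succeed, no split of the threshold and no rule for conflicting results.
- **Treatments** adds, after pill counting, that "participants with less than 80 % compliance will be removed from the study". This filters who can count as having completed.
- **Sample size calculations** does not settle the matter. The number is inflated for 20% dropout, which suggests that the effective analysis is in completers. The same paragraph says that all 182 will be analysed, which suggests intention to treat.
- **Clinical and laboratory evaluations** schedules laboratory tests twice, before and after the 8 days of treatment. A participant who misses the second sample has no post-baseline creatinine.

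**The concern.** The question is one of superiority, and the primary test is to be run in two overlapping populations at the same threshold. If one result is significant and the other is not, the plan gives no reason to prefer either, and the choice would be made with the results in view.

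The two sets are not equally trustworthy. Intention to treat keeps the randomised comparison. The per-protocol set depends on completing and on taking at least 80% of tablets, both of which are determined after randomisation. Patients who become unwell after cisplatin could plausibly miss tablets or the second blood sample, so completion may be related to AKI itself. A difference seen only in completers could then reflect who was left out and not the drug.

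Removal for low compliance may also weaken the intention-to-treat analysis. The article does not say whether day-7 creatinine is still taken from those removed. If it is not, the two sets move towards being the same set of completers under two names.

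**Working it through.** **Inputs.** From Sample size calculations: control AKI incidence 25% ("We expect that the incidence of AKI will be 25 % in patients treated with a single dose of cisplatin"); effect ("treatment with a DPP4 inhibitor could reduce this incidence by 60"%), hence 25% × 0.4 = 10% on gemigliptin; "a one-sided level of significance of α = 5"%; power 80%; dropout 20%; 91 per arm. From Statistical analyses: χ² test, P < 0.05, sidedness not stated, so both versions are shown. Assumption: 20% of each arm do not complete, giving 0.8 × 91 ≈ 73 completers and 18 non-completers per arm.

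**1. The plan's own figure.** The unpooled two-proportion formula, one-sided, gives n = (0.25×0.75 + 0.10×0.90) × (1.645 + 0.842)² / 0.15² = 0.2775 × 6.18 / 0.0225 ≈ 76.3 per arm. Multiplied by 1.2, this is 91.5. The arcsine formula gives 76 × 1.2 = 91.2. The stated 91 is reproduced to within rounding, and it rests on about 76 evaluable participants per arm.

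**2. Type I error if success in either set counted.** The per-protocol set is nested in the intention-to-treat set. With no drug effect, and completion unrelated to outcome, the two test statistics have correlation ρ = √(n_PP / n_ITT). The error is P(|Z_ITT| > 1.96 or |Z_PP| > 1.96). Results by simulation (400,000 trials, 25% AKI in both arms, two-sided):

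| Non-completers per arm with a day-7 value | n_ITT per arm | ρ | Either-set error |
|---|---|---|---|
| 0 of 18 | 73 | 1 | 4.9% |
| 4 of 18 | 77 | √(73/77) = 0.97 | 6.0% |
| 9 of 18 | 82 | √(73/82) = 0.94 | 6.5% |
| 18 of 18 | 91 | √(73/91) = 0.90 | 7.0% |

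The one-sided figure for the last row is 6.9%. The bivariate normal calculation with ρ = √0.8 gives 7.1% two-sided and 6.9% one-sided, which agrees. If missing values were instead filled by a fixed convention, which the article does not state, the two-sided figure at 20% non-completion would be 6.2% (missing counted as no AKI) or 8.0% (missing counted as AKI). Two independent tests would give 1 − 0.95² = 9.75%. The overlap keeps the error below that.

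**3. How often the two sets would disagree.** Take the design effect in completers (25% v 10%) with all outcomes observed.

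- *Non-completers on gemigliptin keep the control risk (an illustration).* The intention-to-treat risk on gemigliptin is (73×0.10 + 18×0.25)/91 = 11.8/91 ≈ 13%. The sets disagree on significance in 17% of trials one-sided and 20% two-sided. In 14% and 17% of trials respectively, per protocol is positive and intention to treat negative. The reverse occurs in about 3%.
- *Non-completers on gemigliptin benefit fully.* The sets disagree in 11% of trials one-sided and 14% two-sided, now mostly with intention to treat positive, because it is the larger set (one-sided power 86% v 79%).

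**The case against.** Four arguments weigh against the point.

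*The article does not say that success in one set is enough.* This is correct. It says that both analyses will be done. If significance in both were required, the two-sided error would be about 2.9% with full outcome capture. A reader might infer that the plan grants two chances of success, or nearly doubles the type I error. The documents support only that no rule is stated, and the overlap of the sets limits the inflation to about 2 points when every non-completer is measured.

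*The upper figure needs non-completers to be measured.* This is also correct. If none has a day-7 value and completers alone are tested, the sets coincide and nothing is inflated. Hence the range.

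*The per-protocol set is more than bare completers, and its being listed first means nothing.* Both parts stand. The compliance rule means that completers also met the 80% threshold, and the order of sentences sets no hierarchy. However, the compliance filter makes the set more selected after randomisation, not less. Nor is per protocol always the easier set in which to find an effect: step 3 shows that it depends on how non-completers fare.

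*This is exploratory phase II work, and a condensed article may leave detail to a fuller document.* The Discussion does use that label, which softens the consequence. But the same section gives the aim as demonstrating whether gemigliptin reduces AKI, and the article itself fixes the two sets, the test and the threshold. Leaving the hierarchy open is therefore a feature of what is stated. The method for missing values is different: an article may leave that to the full protocol or analysis plan, and its absence here is no fault.

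**Conclusion.** The point holds in a limited form. The plan tests the primary outcome in two sets at one threshold, names neither as primary and gives no rule for disagreement. One of the two is selected after randomisation. No other section of the article resolves this.

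The inflation of type I error is modest: about 5–7% two-sided against 5%. That range assumes that success in either set would be claimed, 73 of 91 complete per arm, AKI is 25% in both arms, and completion is unrelated to outcome. Selection bias would come on top and is not quantified here.

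The larger problem is the open choice when the results conflict. Under the design effect this would arise in about 17–20% of trials if gemigliptin non-completers had control risk, and in about 11–14% if they benefited fully. Both are illustrations, since the documents do not say how non-completers would fare. The 20% in the article is a dropout rate, so it should not be read as a non-compliance rate or turned into a claim that the trial is underpowered. That would be a separate sample-size question.

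**What to change.** In Statistical analyses, state that the intention-to-treat comparison of AKI (all randomised participants, in the arm assigned) is the single primary analysis on which the conclusion rests, and that the per-protocol comparison is supportive only, whatever its P value. Add that day-7 creatinine is still to be obtained where possible for participants removed for low compliance, and that they stay in the intention-to-treat analysis. In Sample size calculations, align the sentence on analysing all 182 with this choice.

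The cost is a few sentences of wording and some follow-up samples, with no extra participants. The Trial status section says that recruitment is ongoing, so the change can be made before unblinding. The downside is that the effect estimate and power may be somewhat less favourable than in the per-protocol set if non-completers dilute the effect. No particular imputation method is asked for.

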### Randomization

A research coordinator will conduct the randomization and deliver the study drug. The participants and investigators will be blinded to the treatment assignment. A list of random numbers will be generated by an independent statistician. Eligible participants will be randomly assigned 1:1 to either the treatment group or the control group in accordance with the predefined randomization list with a block size of four. The randomization will be stratified on the basis of the number of times cisplatin is administered (one or more than two) and on the cisplatin dose (< or ≥50 mg/m^2^) and will utilize a randomized block design.

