We have considered the potential interactions between gemigliptin and cisplatin from the beginning of this study. First, cisplatin has no effect on hepatic cytochrome P450 3A4 (CYP3A4) in human liver microsomes [39], while gemigliptin is largely metabolized by CYP3A4 [40]. Second, cisplatin is mainly excreted by the kidney, and its nephrotoxicity is mediated via organic cation transporter 2 (OCT2) in the kidney [1, 41]. Gemigliptin and its active metabolite, LC15-0636, are very weak inhibitors of OCT2 in cultured xenopus oocytes. In terms of metabolic pathways and the renal transport system, cisplatin and gemigliptin never interact. Therefore, the renoprotective effect of gemigliptin could be investigated without affecting the anti-tumor activity of cisplatin.

The dose of gemigliptin in this study is two times higher than the dose used in the treatment of diabetes. Based on previous studies [29, 42], we determined that this dose was necessary to inhibit DPP4 activity by more than 80 % during cisplatin exposure.

DPP4 inhibition has not caused hypoglycemia in studies of healthy volunteers [43, 44]. Because the effects of GLP-1 on insulin secretion are glucose-dependent, the risk of hypoglycemia associated with DPP4 inhibitor treatment is low [45]. Nonetheless, we will exclude the participants with diabetes from this study. Therefore, the risk of hypoglycemia due to gemigliptin administration may be almost negligible in this trial.

A strength of this trial is that we will standardize hydration protocols before, during, and after cisplatin treatment to minimize the effects of confounding variables associated with renal outcomes. Cisplatin dosage per body surface area and the presence of diabetes have been reported to be the risk factors for moderate and severe cisplatin-induced AKI [31]. Another strength of this study is that randomization will be stratified on the basis of cisplatin dosage. Furthermore, participants with diabetes will be excluded from this study.

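### Randomisation is stratified by number of cisplatin administrations and by dose, but the primary chi-square test ignores the strata: conservative and slightly inefficient if the strata predict AKI

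*Protocol article*

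**What the plan says.** - **Design.** Protocol article, Randomization: "The randomization will be stratified on the basis of the number of times cisplatin is administered (one or more than two"). The second stratification factor is dose, split at 50 mg/m². Allocation is 1:1 "in accordance with the predefined randomization list with a block size of four".
- **Primary analysis.** Statistical analyses: "The incidence of AKI will be compared between the two groups using a" chi-square test. No stratified or adjusted comparison is named. The significance threshold is P < 0.05, with no sidedness given.
- **Sample size.** Sample size calculations uses the same test: "We expect that the incidence of AKI will be 25 % in patients treated with a single dose of cisplatin". The assumed effect is a 60% relative reduction. The level is one-sided 5%, power is 80%, dropout is 20%, and the result is 91 per group.
- **Relation of the strata to AKI.** Background cites AKI in 6–35% of patients after a single dose and 50–75% after multiple doses, and calls the renal impairment dose-dependent. The Discussion reports dose per body surface area as a risk factor for moderate and severe AKI and adds: "Another strength of this study is that randomization will be stratified on the basis of cisplatin dosage".

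**The concern.** Blocked randomisation within strata keeps the arms nearly balanced on the stratification factors, so differences in AKI risk between strata contribute little to the difference between arms. The crude chi-square variance still counts those differences as noise. If the strata carry prognostic information, the standard error is too large, the true type I error falls below its nominal level, and some power is lost. The article presents stratification on dose as a strength, yet the named primary test cannot use it. The Discussion also says that enrolling more participants is not feasible, so power that can be recovered by analysis alone is worth having.

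**Working it through.** **1. The plan's own figure.** Inputs from Sample size calculations: 25% against 25% × (1 − 0.60) = 10%, one-sided 5%, power 80%, dropout 20%. The arcsine formula gives 75.9 per group, and 75.9 × 1.2 = 91. The unpooled formula gives 76.3, and 76.3 × 1.2 = 91.5. So 91 is reproduced from a two-group comparison with no strata in it.

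**2. Assumptions.** The article has no stratum rates or shares for this trial. I take 25% AKI after one dose (its sizing rate), 50–75% after multiple doses (its Background range), and a multiple-dose share of 25% or 50% (not in the article). Dose is not modelled separately here.

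**3. Approximation for the crude test with no treatment effect.** For stratum share w and rate p, with overall rate p̄:

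R = Σ w·p(1−p) / [p̄(1−p̄)], two-sided error ≈ 2·[1 − Φ(1.96/√R)].

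- 25% and 60%, half each: R = (0.1875 + 0.2400)/2 ÷ (0.425 × 0.575) = 0.2138/0.2444 = 0.875; error 3.6%.
- 25% and 75%, half each: R = 0.1875/0.25 = 0.75; error 2.4%.

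**4. Simulation.** 200,000 trials per scenario, N = 182, permuted blocks of four within strata. The crude statistic is the difference in proportions over its pooled standard error. The CMH statistic is Σ(expected − observed treated events) / √Σ[n_T·n_C·m(n−m)/(n²(n−1))], where m is the number of events and n the number of participants in a stratum.

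| Multiple-dose AKI, share | Crude type I error, one-sided (two-sided), no dropout | Power at 40% reduction, 20% dropout, one-sided: crude → CMH | Same, two-sided |
|---|---|---|---|
| 50%, 25% | 4.5% (4.4%) | 54.4 → 55.4% | 41.6 → 42.8% |
| 50%, 50% | 4.6% (4.3%) | 63.8 → 65.2% | 51.2 → 52.9% |
| 62.5%, 25% | 4.2% (3.9%) | 59.3 → 62.1% | 46.2 → 49.4% |
| 62.5%, 50% | 3.8% (3.2%) | 73.1 → 76.0% | 61.1 → 65.0% |
| 75%, 25% | 3.5% (3.0%) | 64.3 → 69.3% | 51.2 → 57.2% |
| 75%, 50% | 2.6% (2.1%) | 81.7 → 86.1% | 71.2 → 77.7% |

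The CMH test stays at about 4.9–5.1% throughout. With 20% dropout the crude two-sided error is about 2.8–4.6%.

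**5. Power at the planned 60% reduction, 20% dropout** (multiple-dose rates 50%, 60% and 75%, same shares). Crude power is about 88–99% one-sided and 80–98% two-sided. CMH adds 0.3–1.3 points one-sided and 0.7–2.5 two-sided.

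**6. Weak or no prognostic value.** With 25% against 35%, the CMH gain is zero to within 0.1 point. With four strata all at 25%, CMH costs about 0.4 point (78.5 → 78.1% one-sided, 67.7 → 67.3% two-sided).

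**7. Sensitivity: overall control rate held at 25%, treated rate 10%, 20% dropout.** Four strata at 15–35%: CMH gains 0.2 point one-sided (0.4 two-sided). Strata at 10, 15, 30 and 45%: about 2 points either way. Two strata at 6% and 62.5%: about 7 (11) points. That last split is extreme, and its 6% conflicts with the 25% the article expects after a single dose.

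**The case against.** The case against acting has four parts.

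- **The error is on the safe side.** The crude test does not exceed its nominal level, and a positive result remains valid. The Discussion describes the trial as phase II and exploratory. This stands, and it limits the severity.
- **The prognostic strength in this trial is unknown.** Background gives no time window for the 50–75% figure, whereas the endpoint is assessed at 7 days. Table 1 excludes a history of AKI before randomisation, which could narrow the gap between strata. Dose is reported as a risk factor for moderate and severe AKI, while the endpoint includes a creatinine rise of 0.3 mg/dl. This stands: a reader might infer that the article calls the strata strongly prognostic, but it does not use that strength of language.
- **The loss is easily overstated.** From the variance ratios with no treatment effect (0.80 and 0.75 at 75% multiple-dose AKI), a reader might infer a loss worth 1/0.80 − 1 = 25% to 1/0.75 − 1 = 33% more patients. Under the planned effect the treated strata sit at 0.4 × 25% = 10% and 0.4 × 75% = 30%, so the spread is smaller, and crude power is already high. A reader might also infer that the trial is already short of power. In these scenarios the overall control rate is 31–50%, not 25%, and one-sided crude power at the planned effect is 88–99%, so that inference fails on the plan's own one-sided basis.
- **An unseen analysis plan may add adjusted analyses.** It may, but the article positively names the primary test and sizes the trial on it. This does not remove the mismatch.

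**Conclusion.** The point holds as a modest efficiency issue that should be fixed, not as a threat to validity. The primary test does not use the strata on which the trial is randomised. Under the assumed rates and shares, the two-sided type I error is about 2–4.5% instead of 5%. The power forgone is small at the planned effect and reaches about 5 points one-sided (6.5 two-sided) only if the true reduction is nearer 40% and multiple-dose AKI is near 75%. If the strata barely predict AKI, nothing is gained and at most a fraction of a point is lost. The direction follows from the design. The size depends on stratum rates and shares that the article does not give.

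**What to change.** In Statistical analyses, replace the primary test by a CMH test stratified by number of cisplatin administrations and by dose category, using the strata as randomised. Report a Mantel-Haenszel risk difference with its 95% CI, and keep the crude chi-square test as a sensitivity analysis. State the sidedness of the test. The category wording in Randomization leaves exactly two administrations unplaced, so the strata should be defined without that gap.

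The cost is about one sentence. Both factors are recorded at randomisation, so no new data are needed, and the software named in the article can run the test. Recruitment was still open at publication, so the change could be dated and made before unblinding. The sample size need not change.

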### Outcome measures

The primary outcome of interest is the incidence of AKI at 7 days after cisplatin treatment, where AKI is defined as any of the following: an increase in SCr levels of ≥0.3 mg/dl, an increase in SCr levels of 50 % compared with baseline levels, or a decrease in the eGFR by ≥25 % compared with baseline [31–33]. The secondary outcomes will include changes in SCr levels and the eGFR compared with baseline values for 7 days after cisplatin treatment.

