### Clinical and laboratory evaluations

The physical examination and medication reviews will be conducted before and after 8 days of treatment. Laboratory evaluations will be performed twice, before and after 8 days of treatment; the laboratory evaluations will include a complete blood count; measurements of the levels of hemoglobin, electrolytes, SCr, calcium, phosphorous, protein, albumin, and glucose; a liver function test; and urinalysis. DPP4 activity and the concentration of the DPP4 inhibitor will be measured in serum and plasma after treatment.

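### Changes in creatinine and eGFR are compared without baseline adjustment, which is valid but generally less precise than ANCOVA on data already collected

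*Protocol article*

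**What the plan says.** The protocol article, Outcome measures, defines the outcomes as changes from baseline: "The secondary outcomes will include changes in SCr levels and the eGFR compared with baseline values for 7 days after cisplatin treatment".

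The timing of the values is fixed under Clinical and laboratory evaluations: "Laboratory evaluations will be performed twice, before and after 8 days of treatment". Each patient therefore has one baseline and one follow-up value.

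Statistical analyses gives the method: "The differences in changes in SCr levels and in the eGFR will be analyzed using" one of two tests. The first is Student's t-test, and the alternative is given only as "or the Mann-Whitney *U* test". The threshold follows: "A value of *P* < 0.05 will be considered statistically significant". That section names no baseline covariate, no adjustment for the randomization strata and no rule for choosing between the two tests.

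**The concern.** The article states the method for these outcomes, so it can be judged as written. Subtracting baseline is the same as fixing the slope of follow-up on baseline at 1. If the true slope differs from 1, two things follow. The comparison carries variance that a fitted slope would remove. Also, a chance baseline difference between the arms is over- or under-corrected in the sample actually drawn.

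What is at stake is precision in secondary outcomes. The Discussion says that the institution cannot feasibly enroll more participants, so a more efficient analysis is one of the few ways left to gain precision.

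A smaller point is that the two tests answer different questions. The t-test compares means and the Mann-Whitney test compares ranks, and the latter gives no mean difference in creatinine or eGFR units.

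**Working it through.** **The plan's own figure.** There is none for these outcomes: the document gives no SD, correlation, effect size or power for SCr or eGFR change. The 91 per group in Sample size calculations rests on AKI incidence alone. It can be reached from 25% versus 10%, one-sided 5% and 80% power with the arcsine formula and dropout added as a multiplier (75.87 × 1.2 = 91.0). It has no bearing on this point.

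**Inputs.** From the document: one baseline and one follow-up value, 1:1 allocation, 91 per arm and 20% dropout, so about 91 × 0.8 = 72.8, or 73 per arm. Assumed: the baseline-to-follow-up correlation rho and the ratio k of follow-up SD to baseline SD.

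**Formulas.** Let s0 and s1 be the baseline and follow-up SDs.
- Change score: V_change = s0² + s1² − 2·rho·s0·s1
- ANCOVA: V_ancova = s1²·(1 − rho²)
- Difference: V_change − V_ancova = (s0 − rho·s1)² = s0²·(1 − b)², where b = rho·s1/s0 is the slope of follow-up on baseline.

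The difference is a square, so in large samples ANCOVA is never less precise, and the two are equal exactly when b = 1. Estimating one slope costs about one of 2 × 73 − 2 = 144 degrees of freedom, which is under 1%.

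**Equal variances (k = 1).** V_change = 2s²(1 − rho) and V_ancova = s²(1 − rho²), so the ratio is (1 + rho)/2. The last column shows the power under ANCOVA if a two-sided 5% change-score test had 80%. That 80% is illustrative only.

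| rho | variance ratio | variance saved | equivalent extra patients (1/ratio − 1) | power under ANCOVA |
|---|---|---|---|---|
| 0.5 | 0.75 | 25% | 33% | 90% |
| 0.7 | 0.85 | 15% | 18% | 86% |
| 0.8 | 0.90 | 10% | 11% | 84% |
| 0.9 | 0.95 | 5% | 5% | 82% |
| 0.95 | 0.975 | 2.5% | 2.6% | 81% |

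**Unequal variances.**
- k = 1.4, rho = 0.7 (b = 0.98): 1.96 × 0.51 = 0.9996, against 1 + 1.96 − 1.96 = 1.00. The ratio is 0.9996, so there is no gain.
- k = 1.2, rho = 0.8 (b = 0.96): 1.44 × 0.36 = 0.518, against 1 + 1.44 − 1.92 = 0.520. The ratio is 0.997.
- k = 2, rho = 0.9 (b = 1.8): 4 × 0.19 = 0.76, against 1 + 4 − 3.6 = 1.40. The ratio is 0.543.

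Over k from 1 to 2 and rho from 0.5 to 0.9, the ratio ran from 0.54 to 1.00 and never exceeded 1.

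**The choice between tests.** In 20,000 simulated null trials with 73 per arm, each test alone held about 5%. Always reporting the smaller of the two p-values gave 5.7% with normal data and 7.1% to 7.7% with skewed data.

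**The case against.** The strongest defence is that nothing here is wrong. The outcomes are defined as changes, changes are compared, and under 1:1 randomization the t-test on change is valid and unbiased. A reader might infer from the baseline-imbalance argument that the planned test is biased. It is not: that argument concerns the particular sample drawn, not the validity of the test. This part of the defence stands.

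A reader might also infer a fixed loss equal to 11% to 33% more patients. That range holds only for rho between 0.5 and 0.8 with equal variances, and the documents support neither condition. Variances may well differ, since the plan expects AKI in 25% of patients after a single dose, which would tend to widen follow-up creatinine. As shown, a slope near 1 removes the gain. This also stands, and it limits the size of the point.

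A third tempting reading is that the open choice of test inflates type I error to as much as 7.7%. That figure requires always picking the smaller p-value, which the article does not propose. The conventional reading is a choice based on distribution, and a rule for it is detail that an article may leave to an analysis plan not shown here. The missing rule is therefore not an error in itself, although naming one main analysis would settle it.

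Finally, these outcomes are secondary, the Discussion calls the trial exploratory phase II research, and no stated power claim depends on them. All of this lowers the severity. It does not remove the gain, because the stated method leaves the baseline covariate unused and replacing it carries essentially no loss.

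**Conclusion.** The point holds as a low-cost improvement to the secondary analyses, not as a validity failure. The planned comparison of raw changes is unbiased but generally less precise than ANCOVA on the same data. Under equal variances and rho of 0.5 or more, the saving is at most about 25% of variance. It is 10% at rho 0.8, 5% at rho 0.9, and tends to nil as rho approaches 1. With unequal variances it is about nil when the slope is near 1 and can be larger when the slope is far from 1. Rho and the SD ratio are assumptions, because the document gives neither. The primary outcome and its sample size are unaffected.

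**What to change.** Before unblinding, replace the sentence on the secondary outcomes with one main analysis for each: ANCOVA of the day-7 value (or of the change, which gives the same treatment estimate) in SCr and in eGFR, on treatment and baseline value. Report the adjusted mean difference with a 95% CI. This keeps the effect measure on the scale that Outcome measures names.

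Add the randomization strata as covariates once the Randomization section is clarified. As worded, its categories for the number of cisplatin administrations leave a patient with exactly two unassigned.

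Name the Mann-Whitney test as a sensitivity analysis, and an analysis of log SCr as another if the data are skewed. Log SCr changes the effect measure to a ratio, so it should not silently replace the main analysis.

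The cost is wording, plus resolving the stratum definition. No new data are needed, and Trial status says that recruitment is still under way.
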